### Safety

Clinical governance for trial participants rests with the service to which they are allocated (Orygen Youth Health or *headspace*). Treatment continues for approximately 26 weeks, unless the participant meets the trial’s withdrawal criteria. Withdrawal from the trial’s treatment program will occur if:Participation in the study interferes with the appropriate clinical management of risk of self-harm or harm to others. This decision is initiated by the treating clinical team, in consultation with the principal investigator.The participant meets the operational criteria for Orygen Youth Health’s first-episode psychosis program, or DSM-IV operational criteria for bipolar I or II disorder. These will be assessed by an independent psychiatrist (or trainee psychiatrist).Consent is withdrawn

### Data integrity

The research assistants who conduct follow-up assessments are psychology graduates who are trained and supervised by the chief investigator/consultant psychiatrist and the trial coordinator/clinical psychologist. Assessment interviews are audio recorded, and ten percent of assessments at each time point are randomly selected for inter-rater reliability.

Data entry verification is undertaken on a randomly selected twenty percent of cases at each time point, with an *a priori* acceptable rate of 0.5 %. The statistician who will perform the analyses is also blind to treatment group allocation.

### Statistical analyses and sample size determination

To determine whether there are group differences on the primary and secondary outcome measures at 12 months, a series of mixed effects model repeated measures analysis of variances models (MMRM) will be employed. The within groups factor will be time, and the group will serve as the between subjects factor. MMRM is a preferred method for analysing clinical trial data in psychiatry in comparison with the more traditional repeated measures analysis of variance and analysis of covariance models [55]. MMRM is advantageous because it includes all existing data in the model, there is no imputation or substitution of missing data, dispersion and correlation can occur at all time points, and sensitivity analysis can be successfully conducted. Within these models, planned comparisons will be used to determine whether HYPE + CAT is superior to the other two interventions, and whether the HYPE service model leads to better outcomes compared with YMHS.

Power and sample size calculations have been based on a one-way analysis of covariance model with baseline values as the covariate, and the outcome measures as the dependent variables. It is assumed that the baseline covariate will account for 50 % of the variance in an outcome measure. Based on our published data [29, 56], we expect to find medium treatment effects on the primary outcome measures of interpersonal problems and social adjustment. Alpha has been set at 0.05 and power (1-β) for the study at 0.80. Given these parameters, we require 40 participants per group (120 in total) with at least two data points. Based upon the 14 % attrition rate in our previous randomised control trial we intend to recruit at least 45 cases per group.

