Participants are invited to participate by the trial coordinator, who contacts the young person (and their parent or legal guardian for those under 18 years) to introduce the study and to offer an appointment to obtain written consent. After the trial coordinator obtains written consent, a research assistant or the trial coordinator conducts the baseline assessment. All participants receive assertive case management, crisis care and general psychiatric care during the pre-screening and assessment phase. Once eligibility for the trial is confirmed, the trial coordinator randomly and consecutively assigns participants to one of the three interventions in a ratio of 1:1:1 using a password-protected computer program with a randomisation sequence that was computer-generated by an independent statistician. Treatment allocation uses randomised permuted blocking, and participants are stratified by age (cut point of age 18 years), sex and the Centre for Epidemiological Studies Depression Scale Revised (CESD-R) [35] score (cut point = 37, which is the mean score for borderline personality disorder patients on entry to HYPE), thus minimising these potentially confounding factors. Following randomisation to a treatment group, the trial coordinator then randomly assigns participants to the next available trial clinician using a separate randomisation sequence that was also computer-generated by an independent statistician. The trial coordinator contacts the participant and the treating service to inform them of the treatment group and clinician allocation. The clinician then contacts the participant to arrange the first appointment. Thus, the trial coordinator conducts the consent and randomisation procedures separately from the blinded research assistants, using independently derived, password-protected, computer-generated randomisation sequences.

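### The 40 per group is sized on an ANCOVA in which baseline removes half the variance, but the MMRM described names only time and group, so the stated 80% power may not hold for the planned 12-month comparison

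*Protocol article*

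**What the plan says.** Both statements stand in the protocol article under *Statistical analyses and sample size determination*.

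- **Analysis.** Group differences at 12 months on the primary and secondary outcomes are to be examined with an MMRM: "The within groups factor will be time, and the group will serve as the between subjects factor". Planned comparisons within that model test HYPE + CAT against the other two interventions, and HYPE against YMHS. The text prefers the MMRM to traditional repeated-measures ANOVA and to ANCOVA.
- **Sample size.** The model is named as follows: "Power and sample size calculations have been based on a one-way analysis of covariance model with baseline values as the covariate". The allowance made for that covariate is explicit: "It is assumed that the baseline covariate will account for 50 % of the variance in an outcome measure". The effect size is described only as medium, for both primary measures. The significance level is 0.05 and the target power 0.80. The result: "we require 40 participants per group (120 in total) with at least two data points".

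Table 1 lists both primary measures, IIP-C and SAS-SR, at baseline and at 3, 6, 12 and 18 months. The article does not say whether baseline is a level of the time factor, a covariate, or a response with a mean common to the arms. Nor does it say whether the 12-month comparison is of levels or of change.

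**The concern.** The 50% variance credit comes from conditioning on baseline. A model with only time and group does not necessarily condition on it. If baseline is one level of time and each arm has its own baseline mean, the arm difference at 12 months is, with complete data, the raw difference in 12-month means. Having baseline in the data set then does not reduce its variance.

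Two things are at stake. The planned comparisons may have less power than the sample-size statement promises. A comparison of 12-month levels would also be exposed to chance baseline imbalance on IIP-C and SAS-SR with about 45 per arm. Randomisation is stratified by age, sex and CESD-R score, not by either primary measure.

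**Working it through.** **Inputs from the article:** α = 0.05 (taken as two-sided for contrasts), target power 0.80, R² = 0.50 for baseline, three arms allocated 1:1:1, n = 40 per arm (N = 120).

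**Assumption:** medium is not quantified. I take arm means of −0.25, 0 and +0.25 SD, so f² = (0.0625 + 0 + 0.0625)/3 = 0.0417 and f = 0.204. This value is chosen because it returns the article's sample size.

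**1. Reproduce the stated figure.** For the ANCOVA, λ = N·f²/(1 − R²) = 120 × 0.0417/0.50 = 10.0 on (2, 116) df. Power is 0.805, and 40 per arm is the smallest n that reaches 0.80. The stated figure therefore depends on the baseline credit.

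**2. Variance under each handling of baseline.** R² = 0.50 implies a baseline to 12-month correlation r = √0.50 = 0.707. In units of the outcome variance:

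- baseline as covariate, or common baseline mean: 1 − r² = 0.50
- change from baseline: 2(1 − r) = 0.586 (equal variances at both times)
- 12-month levels, arm-specific baseline means: 1.00

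**3. Omnibus power at 40 per arm**, with λ = 5.0/variance:

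| Baseline handling | λ | Power | n per arm for 0.80 |
|---|---|---|---|
| Covariate / common mean | 10.0 | 0.805 | 40 |
| Change from baseline | 8.54 | 0.735 | 47 |
| 12-month levels, unconstrained | 5.0 | 0.493 | 79 |

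**4. Contrasts at 0.5 SD**, two-sided 0.05, non-central t with SE = √(variance × Σc²/40). Σc² is 2 for a pair and 1.5 for one arm against the average of the other two.

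| Baseline handling | Pairwise | HYPE + CAT vs other two averaged |
|---|---|---|
| Covariate / common mean | 0.880 | 0.952 |
| Change from baseline | 0.826 | 0.917 |
| 12-month levels, unconstrained | 0.602 | 0.726 |

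**5. Does including baseline as a level of time restore the credit?** I computed the generalised least squares variance of a pairwise 12-month difference, with five time points, 45 per arm and compound symmetry at r = 0.707 (an assumption; the article states no covariance structure).

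- Complete data: 0.0444 with arm-specific baseline means, 0.0222 with a common mean; ratio 2.0.
- 14% missing at 12 and 18 months: 0.0472 against 0.0250; ratio 1.89.

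So it does not, for a contrast of levels. A covariate or a common baseline mean restores the credit in full, and a change contrast restores most of it.

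**6. Sensitivity to the reading of medium.** With f = 0.25, omnibus power at 40 per arm is 0.94, 0.90 and 0.68 in the order of the tables. With one arm 0.5 SD from two equal arms (f = 0.236) it is 0.91, 0.86 and 0.62.

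**The case against.** The strongest reply is that the article leaves the role of baseline open. The sentence on the model names factors; a continuous baseline score is not a factor, so its absence there does not exclude it as a covariate. Covariates and contrast coding are commonly settled in a SAP, which is not shown here. If baseline is a covariate, or a response with a common mean, nothing is lost. This stands, and it is why the shortfall is conditional.

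Two further parts also stand. The effect size is back-solved, and on larger readings of medium the change contrast exceeds 0.80. Inference is by planned comparisons, so 0.49 is the power of the test that reproduces the sample size and not of those contrasts. On 12-month levels, though, the two contrasts computed at 0.5 SD (0.60 and 0.73) still fall below 0.80.

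A reader might infer that the trial does not have 80% power, or that baseline has been left out of the analysis. The article supports neither: it fixes no baseline handling from which a shortfall would follow.

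One part of the reply fails. The use of all existing data, the requirement of at least two data points and the baseline column in Table 1 all allow baseline to be a repeated measure. Step 5 shows that this alone does not recover the 50% for a comparison of levels. Nor is the point merely about an omitted detail: the article gives two models, one for sizing and one for analysis, and does not connect them.

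**Conclusion.** The point holds as a mismatch between the sizing model and the described analysis model. The 80% is the power of an ANCOVA with baseline as covariate; whether the MMRM delivers it depends on a choice the article does not state. On the test that reproduces 40 per group, the loss runs from none (0.805), through about 7 points for change from baseline (0.735), to about 31 points for 12-month levels with arm-specific baseline means (0.493). A pairwise 0.5 SD difference analysed as change stays above target, at 0.83.

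These figures rest on R² = 0.50 as stated, f = 0.204 or a 0.5 SD contrast as assumed, equal variances at baseline and 12 months for the change contrast, and 40 evaluable per arm. The described aim, group differences in outcomes at 12 months, reads most naturally as a contrast of levels, which is the costly case, but the text does not settle it.

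**What to change.** State the MMRM in full before unblinding. Use the 3-, 6-, 12- and 18-month scores as responses, with group, time, group-by-time, baseline score and baseline-by-time in the model. Alternatively, keep baseline as a response and constrain its mean to be equal across arms. Say that the planned comparisons are tested at 12 months from the group-by-time terms. If the full protocol or SAP already does this, cite it beside the sample-size paragraph.

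The cost is a sentence or two of analysis-plan text. Both primary measures are already scheduled at baseline, so no new data or participants are needed. The change aligns the analysis with the model that justified 40 per group and adjusts for chance baseline imbalance on IIP-C and SAS-SR. The same sentence should give the medium effect as a number and name the contrast it refers to, so that the calculation can be checked without back-solving.

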### Aims and hypotheses

The overall purpose of this study is to evaluate the effectiveness of three forms of early intervention for adolescents and emerging adults (youth) with borderline personality disorder. The three early interventions vary in their degree of complexity, as determined by different components of service delivery (HYPE versus a general youth mental health service (YMHS)) and individual psychotherapy (CAT versus befriending (BEF)). The three early interventions are (in order of increasing complexity): YMHS + BEF, HYPE + BEF, and HYPE + CAT. The findings of this trial will help to clarify the level and complexity of services and treatments required for effective early intervention for borderline personality disorder.

The specific study aims are to: (i) elucidate whether a specialist early intervention service (HYPE) in addition to CAT (HYPE + CAT) will lead to superior outcomes as compared with the HYPE + BEF and the YMHS + BEF interventions; and (ii) determine whether there is a difference in effectiveness between the HYPE and YMHS service models.

The primary hypothesis is that at the 12-month primary endpoint participants receiving HYPE + CAT will have better outcomes on the primary (social adjustment and interpersonal problems) and secondary (borderline personality disorder symptoms, suicidal ideation, self-injury, depression, alcohol and substance use) outcome measures than those in the HYPE + BEF and YMHS + BEF interventions.

A secondary hypothesis is that at the 12-month primary endpoint, those treated with the HYPE model will have better outcomes on primary and secondary outcome measures than those young people being treated with the YMHS model.

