## Methods

### Study design

This study is a parallel group, single-blind RCT comparing three groups: HYPE + CAT, HYPE + BEF, and YMHS + BEF. A full factorial design ( that is, including a fourth treatment arm comprising YMHS + CAT) was not implemented in order to meaningfully differentiate HYPE from YMHS. The HYPE service model incorporates the theory and principles of CAT, without CAT necessarily being used as an individual therapy. This is a key point of differentiation from usual youth mental health service models. If CAT were introduced at the YMHS site it would change usual YMHS practice (that is, the YMHS would represent a specialised rather than generalised service), thus limiting the external validity of this intervention.

The study design was developed in accordance with Good Clinical Practice (GCP) Guidelines and Standard Protocol Items; Recommendations for Interventional Trials (SPIRIT [30]). Figure 1 summarises the trial design. The trial is registered with the Australian New Zealand Clinical Trial Registry (ACTRN12610000100099) and has been approved by the Melbourne Health Human Research Ethics Committee (HREC2010.055).

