## Discussion

The current trial extends previous research and addresses the following questions. What is the comparative effectiveness of three different levels of complexity of early intervention for borderline personality disorder? What is the comparative effectiveness of a specialised early intervention service model over and above general youth mental health care in early intervention for borderline personality disorder? What is the contribution of individual cognitive analytic therapy over and above specialised general clinical care in early intervention for borderline personality disorder? Is early intervention for borderline personality disorder effective for emerging adults as well as for adolescents?

In order to answer the above questions, the trial separately evaluates early intervention, independent of indicated prevention, by only including full-syndrome borderline personality disorder. This has an added advantage of reducing heterogeneity among the sample. The trial also extends the age range of new onset cases studied from 15–18 to 15–25 years. It also focuses upon functional outcomes, reflecting recent findings that this aspect of borderline personality disorder is stably poor over long-term follow-up, refractory to current treatments, and should be the primary focus of treatment outcome studies for borderline personality disorder [6, 12, 14].

While the trial design has attempted to address many problems identified in previous studies, some problems are anticipated. Safety measures for the trial mean that participants who drop out of the trial intervention but who require continuing treatment in a mental health service will be eligible for referral to Orygen Youth Health, meaning that they might receive HYPE + CAT, which is the default treatment offered at Orygen. This will be examined in secondary analyses.

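### Read literally, the secondary HYPE-versus-YMHS comparison includes the HYPE + CAT arm, so it estimates the service effect plus half the CAT effect

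*Protocol article*

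**What the plan says.** The section on statistical analyses and sample size in the protocol article names two planned comparisons within the mixed models. The first is that "planned comparisons will be used to determine whether HYPE + CAT is superior to the other two interventions". The second is "whether the HYPE service model leads to better outcomes compared with YMHS". No contrast weights are given, and the text does not say whether arms are averaged.

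Aims and hypotheses gives the second comparison its population: "those treated with the HYPE model will have better outcomes on primary and secondary outcome measures" than young people treated under YMHS. The Setting section places both HYPE + CAT and HYPE + BEF at the HYPE Clinic. The Study design section explains why a full factorial, "including a fourth treatment arm comprising YMHS + CAT", was not used.

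The questions to be answered are about components. Aim (ii) asks whether the two service models differ in effectiveness. The Discussion asks what the specialised service adds to general care and, separately, "What is the contribution of individual cognitive analytic therapy over and above specialised general clinical care".

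**The concern.** With no YMHS + CAT arm, CAT appears only on the HYPE side. If both HYPE arms enter the service comparison, half of that side has had CAT and none of the YMHS side has. The result then carries part of any CAT effect and cannot be read as the effect of the service model.

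This matters for the use the authors foresee. The Discussion ties the service answer to whether specialised services should be built or general youth services scaled up. It ties the CAT answer to whether clinicians need the two-year CAT training. A comparison that credits the service with a gain produced by CAT would point both decisions the wrong way.

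**Working it through.** **Inputs.** From the sample-size section: 40 per arm and 120 in total; "Alpha has been set at 0.05 and power (1-β) for the study at 0.80"; "It is assumed that the baseline covariate will account for 50 % of the variance in an outcome measure"; and "we expect to find medium treatment effects on the primary outcome measures of interpersonal problems and social adjustment". Assumed here: a two-sided test, since sidedness is not stated, and component effects of 0.25 to 0.8 SD, since medium is given no number. The calculation uses the analysis-of-covariance model on which the trial was sized.

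**The plan's own figure.** For a three-group analysis of covariance with one covariate, the noncentrality is N·f²/(1 − R²). Take 0.5 SD between the extreme arms with the middle arm halfway. Then f = 0.5/√6 = 0.204, the noncentrality is 120 × 0.0417/0.5 = 10.0, and power is 0.805, so 40 per group is reproduced. This reading is not the only possible one: f = 0.25 with R² = 0.5 would need only 27 per group. On the reading that matches, neighbouring arms differ by 0.25 SD.

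**What each contrast estimates.** Let the 12-month means, scored so that higher is better, be 0 for YMHS + BEF, s for HYPE + BEF and s + c for HYPE + CAT.

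- Mean of both HYPE arms minus YMHS + BEF: (s + s + c)/2 = s + c/2
- HYPE + BEF minus YMHS + BEF: s
- HYPE + CAT minus HYPE + BEF: c
- HYPE + CAT minus the mean of the other two: (s + c) − s/2 = c + s/2

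**Standard errors.** The residual SD is √(1 − 0.5) = 0.707.

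- Pooled: 0.707 × √((0.25 + 0.25 + 1)/40) = 0.137 SD
- Two-arm: 0.707 × √(2/40) = 0.158 SD
- Ratio: √(2/1.5) = 1.155

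**Pooled HYPE against YMHS when the service does nothing (s = 0).** The probability of a significant result favouring HYPE comes from the noncentral t with 120 − 3 − 1 = 116 degrees of freedom and critical value 1.98.

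| CAT effect c | Contrast c/2 | Noncentrality, R² = 0.5 | Probability, R² = 0.5 | Probability, R² = 0 |
|---|---|---|---|---|
| 0.25 SD | 0.125 | 0.91 | 0.15 | 0.09 |
| 0.3 SD | 0.15 | 1.10 | 0.19 | 0.12 |
| 0.5 SD | 0.25 | 1.83 | 0.44 | 0.25 |
| 0.8 SD | 0.40 | 2.92 | 0.83 | 0.54 |

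HYPE + BEF against YMHS + BEF would favour HYPE with probability 0.025 in every row.

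**Power of the two-arm contrast at 40 per arm.** At 0.5 SD, 0.5/0.158 = 3.16 gives power 0.88 (0.60 if baseline explains nothing). At 0.3 SD power is 0.47. At 0.25 SD, 0.25/0.158 = 1.58 gives 0.35.

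**The HYPE + CAT comparison when CAT does nothing (c = 0, s = 0.5 SD).** The probability of declaring HYPE + CAT superior depends on how the sentence is read.

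| Reading | Probability |
|---|---|
| Must beat each of the other two arms | 0.025 |
| Must beat their average | 0.44 |
| Beating either arm is enough | 0.88 |

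**The case against.** The strongest reply is that the article never says arms are pooled, and that contrast weights belong in an analysis plan not shown here. As to weights, that is right: their absence is no fault. The point rests on the wording that is present. The secondary hypothesis defines its group by treatment under HYPE, both HYPE arms meet that definition, and nothing restricts it to HYPE + BEF. An analysis plan that followed the hypothesis as written would produce the mixed contrast.

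It can also be said that a pooled contrast answers a sensible policy question, since the article describes HYPE as usable with or without CAT. That stands, but it is a question about packages and not the service-model question in aim (ii).

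Three stronger readings are tempting, and the article does not support them.

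- *That neither planned comparison isolates its component.* Aims and hypotheses names HYPE + BEF and YMHS + BEF individually as comparators for HYPE + CAT, so superiority to the other two plausibly means superiority to each. That includes HYPE + CAT against HYPE + BEF, which isolates CAT.
- *That the design is at fault.* The three arms contain both clean contrasts, and the omission of the fourth arm is explained.
- *That the false-credit rate is 44%.* That figure needs pooling, no service effect and a CAT effect of 0.5 SD. On the reading that reproduces 40 per group, CAT adds 0.25 SD and the figure is about 15%.

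**Conclusion.** The concern holds for the secondary comparison as worded. With equal weights, which 1:1:1 allocation implies, HYPE against YMHS estimates s + c/2 and not the service effect s. If the service adds nothing, the chance of declaring HYPE better is about 15%, 19% or 44% for CAT effects of 0.25, 0.3 or 0.5 SD. It is 12% at 0.3 SD and 25% at 0.5 SD if the covariate explains nothing. These figures assume 40 analysed per arm and a two-sided 5% level, with effect sizes chosen here.

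For the HYPE + CAT comparison the finding is conditional. It is confounded only if the two comparators are averaged, and the sentence leaves that open.

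**What to change.** Before unblinding, state the following for the 12-month time point:

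1. The service-model test is HYPE + BEF against YMHS + BEF.
2. The test of CAT is HYPE + CAT against HYPE + BEF.
3. HYPE + CAT is called superior to the other two only if separate tests against HYPE + BEF and against YMHS + BEF both succeed.
4. Any contrast that pools the HYPE arms is labelled *HYPE, with or without CAT* and is not used as evidence on the service model alone.

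The secondary hypothesis should be reworded to match item 1. No arm, participant or measurement is added. The price is precision: the service test has a standard error about 15% larger than the pooled one. Power stays at 0.88 for 0.5 SD but is 0.47 at 0.3 SD and 0.35 at 0.25 SD, so a null service result should be reported with its confidence interval and not read as equivalence.
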